### Aim

The aim of the planned study is to investigate the effects of an Internet-based stepped care model, comprising IS and CBT, on levels of anxiety, depression and health-related quality of life in adults with cancer and with symptoms of depression and/or anxiety. Further, the aim is to evaluate the health economic aspects of the intervention. Stepped care will be compared with standard care in a randomized study design.

### The main research questions

#### *Primary research question*

• Do participants who receive Internet-based stepped care report lower levels of anxiety and/or depressive symptoms at 10 months after randomization compared with participants receiving standard care? See details under “Statistical power” below.

#### *Secondary research questions*

• Will participants who report anxiety and/or depression symptoms at diagnosis and who receive Internet-based stepped care report lower levels of anxiety, depression, post- traumatic stress and improved health-related quality of life in the short and long term (≤24 months after diagnosis)?

• Is Internet-based stepped care cost-effective or at least cost-neutral compared with standard care at 10 and 24 months after diagnosis?

• To what extent do participants use the IS skills and strategies suggested for countering symptoms?

## Methods

The present project is part of the Uppsala University psychosocial care programme (U-CARE), an interdisciplinary programme which is being conducted in close collaboration between researchers in clinical psychology, information systems, nursing sciences, medical sciences and economics. An Internet platform (the U-CARE portal) has been developed within the U-CARE programme. The U-CARE portal is used for interventions and data collection in all projects undertaken within the framework of the research programme.

### Design

The present project comprises a prospective randomized controlled trial where stepped care will be compared with standard care. Figure 1 provides an outline of the trial design.

**Figure 1 F1:**
[figure not shown]
**Flowchart of the study.** ICBT = Internet-based cognitive behavioral therapy.

### Participants

Inclusion of patients will start in March 2013 and will continue for approximately 18 months. Patients with newly (within 6 months) diagnosed early-stage breast, prostate or colorectal cancer as well as patients with recurrence of colorectal cancer (within 6 months of diagnosis) at three hospitals in Sweden will be asked to participate in the study. Exclusion criteria are inability to read and understand Swedish, cognitive disability (such as dementia or psychosis), a constant need of care (Karnofsky score <40), short expected survival (<3 months), severe depression or suicide risk with regard to answers on the Montgomery-Åsberg Depression Rating Scale – Self-Report (MADRS-S) measure (see “Data collection” below), and participation in a competing clinical trial including prostate cancer patients receiving radiotherapy. In our previous randomized controlled intervention study on quality of life aspects, approximately 70% of eligible patients agreed to participate, and about 70% of these completed participation [2]. There is a risk that a greater proportion of patients will refuse to take part in the present project since it requires access to the Internet, a mobile phone and some computer skills.

### Statistical power

The main outcome measure is the Hospital Anxiety and Depression Scale (HADS) [27]. It consists of 14 questions divided into one subscale for anxiety symptoms (seven questions) and one for depressive symptoms (seven questions). Both are 21-point scales. Values <7 points on any of the subscales indicate mild anxiety or depression. Values < 10 points indicate clinically significant levels of anxiety and depressive symptoms. A change of at least 20% on the HADS is considered to be a clinically relevant change [28]. In one previous study of patients with <7 points cut-off on any of the HADS subscales, the mean score for anxiety was 10 and for depression, 8 [6]. To achieve 80% statistical power (alpha = 0.05) needed to detect a mean difference of 2.0 points on the anxiety subscale and 1.6 points on the depression subscale, 65 patients are required in each of the intervention and control groups. Based on experience from previous intervention studies, we estimate that approximately 30% of study participants will not complete the data collection. This means that we need to include at least 95 patients in each group. For the present study, approximately 1,300 patients need to be enrolled, <300 of whom are likely to have anxiety or depression symptoms, <200 of whom can be expected to complete the study.

Patients with <7 points on any of the subscales will be allocated to a reference group and answer questionnaires at baseline and at three observation points during the time of the intervention. They will answer questionnaires that measure anxiety, depression and health-related quality of life.

### Randomization

Participants with anxiety and/or depressive symptoms (<7 on any of the HADS subscales) will be randomized to either Internet-based stepped care or standard care. Randomization will be stratified for curable/non-curable disease and will be done in blocks.

Representatives from patient organizations have contributed to the design of step 1 of the intervention and will participate in the discussion forum. This is because there must be a relevant content in the discussion forum when the first participants in the randomized controlled trial begin using step 1. Representatives from patient organizations have also participated in tests regarding the usability of the portal.

### Cognitive behavior therapy – step 2

The Internet-based CBT in step 2 consists of standard CBT programmes for psychological problems. At the beginning of treatment in step 2, participants will receive a list of treatment modules regarding sleeping problems, depression, etc and will be able to choose the problem area/s they want to work with. The treatment is highly structured. It follows established treatment manuals and includes exercises, assignments, self-monitoring and weekly contact with a psychologist over the Internet. A participant who does not follow the treatment plan is reminded and encouraged to participate in the programme; however, it is not mandatory to complete the treatment. In total, step 2 consists of 10 weeks of intervention followed by evaluation. Participants cannot repeat step 2. After finishing step 2, participants have, however, access to the material for the remainder of the study period.

### Standard care

Standard care includes the basic information always provided in routine health care, i.e. information about the disease, the treatment that the patient will undergo, possible side effects of the treatment, and what the patient can do to prevent and relieve symptoms and side effects. Information on existing psychosocial support is given to all patients by the physician or nurse in charge. Psychosocial support activities include, on an as-needed basis, the opportunity to talk to a social counsellor or deacon/priest from the hospital church and, occasionally, to support groups. If the need for help with anxiety or depression is identified, patients are encouraged to raise the problems with the physician responsible for the treatment, for further action which might include pharmacological treatment of anxiety and depression, general support and referral to mental health care.

### Data collection

All patient-reported data will be collected through the U-CARE platform. Well-known questionnaires with good psychometric properties will be used. Table 1 presents an outline of questionnaires and observation points.

**Table 1 T1:** Summary of the study’s instruments and the observation points at which they will be used

**Instrument**	**Observation points**
HADS	At baseline and at 1, 4, 7, 10, 18 and 24 months
MADRS-S	At baseline and at 10 months
STAI-S	At baseline and at 10 months
ESSI	At baseline
NLEs	At baseline
EROS	At baseline and at 10 months
PCL-C	At baseline and at 10, 18 and 24 months
EORTC QLQ-C30	At baseline and at 1, 4, 7, 10, 18 and 24 months
EORTC QLQ-BR23^1^	At baseline and at 1, 4, 7, 10, 18 and 24 months
EORTC QLQ-PR25^1^	At baseline and at 1, 4, 7, 10, 18 and 24 months
EORTC QLQ-CR29^1^	At baseline and at 1, 4, 7, 10, 18 and 24 months
FACIT-F	At baseline and at 1, 4, 7, 10, 18 and 24 months
ISI	At baseline and at 1, 4, 7, 10, 18 and 24 months
PTGI-SF	At 10 months
Health economic questionnaire	At 1, 4, 7, 10, 18 and 24 months
EQ-5D	At 2 weeks and 1, 4, 7, 10, 18 and 24 months
Patient satisfaction questionnaire	At 1, 4 and 10 months
Internet use questionnaire	At 1, 4, 7, 10, 18 and 24 months
Knowledge and strategies questionnaire	At 2 weeks and 1 and 10 months

*EORTC QLQ* European Organization for Research and Treatment of Cancer (EORTC) Quality of Life Questionnaire, *EQ-5D* Euroqol 5D, *EROS* Environmental Reward Observation Scale, *ESSI* Enriched Social Support Inventory, *FACIT-F* Functional Assessment of Cancer Therapy: Fatigue, *HADS* Hospital Anxiety and Depression Scale, *ISI* Insomnia Severity Index, *MADRS-S* Montgomery-Åsberg Depression Rating Scale – Self-Report, *NLEs* Negative Life Events questionnaire, *PCL-C* Post-Traumatic Stress Disorder (PTSD) Checklist – civilian version, *PTGI-SF* Post-Traumatic Growth Inventory, Short Form, *QLQ-Br25* Quality of Life Questionnaire with diagnosis-specific modules for breast cancer, *QLQ-C30* Quality of Life Questionnaire, Core 30, *QLQ-CR29* Quality of Life Questionnaire with diagnosis-specific modules for colorectal cancer, *QLQ-PR25* Quality of Life Questionnaire with diagnosis-specific modules for prostate cancer, *STAI-S* State-Trait Anxiety Inventory – State anxiety subscale.

^1^ = if appropriate.

### Anxiety and depression

The HADS [27] is used as a short screening instrument for symptoms of anxiety and depression and for evaluating the effects of the Internet-based stepped care. The HADS has been used extensively both clinically and in cancer care research and has good psychometric properties [29]. It has been successfully administered via the Internet in other projects [30]. The MADRS-S [31,32] is used as a screening instrument for severe depression and/or suicide risk. It has shown good ability to identify depressive symptoms [33] and it will be used in this study to measure symptoms of depression at inclusion and 10 months after inclusion. The MADRS-S consists of nine questions with response scores of 0–60 points, where values <30 points are considered to indicate severe depression. The MADRS-S includes an item connected with suicidal ideation, where scoring ≥3 on this item is considered to be an indication of present suicide risk. Participants scoring ≥3 on this item will be contacted by one of the psychologists of the project and offered adequate help. The Spielberger State-Trait Anxiety Inventory – State anxiety subscale (STAI-S) [34] will be used to measure anxiety at inclusion and 10 months after inclusion. It consists of 20 questions and has good ability to identify anxiety problems in both younger and older patients [35]. The STAI-S has been administered via the Internet in research.

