#### *Main study*

Eligible patients at the oncology, urology and surgery clinic will be identified and asked for informed consent at a regular visit to the clinic within 6 months after initial diagnosis or detection of disease relapse.

First, participants will be asked to answer all the study’s questionnaires via the U-CARE portal. Patients with severe depression or suicide risk (as measured by the MADRS-S, see “Data collection”) at inclusion or at the 10-month measurement will be excluded from the project and contacted via telephone by a project staff psychologist. Likewise, patients will be contacted by a psychologist if there is reason to believe that they have severe depression or are suicidal according to what they write in the forum or diary or what they post on the chat. Participants in the intervention group will have access to IS immediately after randomization. Both the intervention and the control group will receive the psychosocial support as part of the standard care at their respective clinic. Both groups will answer a set of questionnaires at observation points described in Table 1. The reference group will answer a set of questionnaires at some of the observation points. The patients will be notified by e-mail of when it is time to answer questionnaires. If they do not complete the questionnaires they will be reminded by e-mail 7 days after baseline and after 7 and 12 days after any of the observation points.

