### Ethical aspects

The project has been approved by the Regional Ethical Review Board in Uppsala (Dnr 2012/003). Written informed consent will be obtained from the participants before inclusion. Extensive measures have been taken, and will continue to be taken, to minimize the risk of infringing activities and to ensure that study participants’ personal data cannot be linked to patient-reported data by unauthorized persons. Study participants may at any time terminate participation without giving any explanation. The literature does not suggest that Internet-based support interventions have any negative effects. Rather, there is good reason to assume that different types of Internet-based support and treatment with CBT may be effective for treatment of psychological problems. The main ethical risk is including participants with a need for other specialized medical care, such as those with severe depression. The baseline measurement is designed to minimize that risk. All study participants will also have an established contact with physicians in routine health care.

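### The printed MADRS-S total cut-off for severe depression runs opposite to the suicide item on the same scale, and exclusion and safety contact depend on it

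*Protocol article*

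**What the plan says.** All references are to the protocol article.

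- **Purpose of the scale.** The Anxiety and depression section says the MADRS-S "is used as a screening instrument for severe depression and/or suicide risk".
- **Range.** The same section describes "nine questions with response scores of 0–60 points".
- **Total-score threshold.** It then states that "values <30 points are considered to indicate severe depression".
- **Item threshold.** For the suicidal-ideation item, "scoring ≥3 on this item is considered to be an indication of present suicide risk". Participants who reach that score are to be contacted by a project psychologist.
- **Use at entry.** The Participants section lists among the exclusions "severe depression or suicide risk with regard to answers on the Montgomery-Åsberg Depression Rating Scale – Self-Report (MADRS-S) measure" and sends the reader to Data collection for the details.
- **Use at two time points.** The Main study section says that patients with severe depression or suicide risk "at inclusion or at the 10-month measurement will be excluded from the project" and telephoned by a psychologist. Table 1 schedules the MADRS-S at baseline and 10 months only.
- **Role as a safeguard.** Ethical aspects names the inclusion of patients who need other specialised care, such as those with severe depression, as the main ethical risk, and adds: "The baseline measurement is designed to minimize that risk".

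No section gives another cut-off for the total or says that the total is reverse-scored.

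**The concern.** Two thresholds are set on one questionnaire, and they point in opposite directions. On the suicide item, risk begins at a score and continues upward. On the total, as printed, severe depression lies below a score and continues downward to 0. The text offers nothing, such as reverse scoring, that would let both hold.

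This is an operating rule and not background description. It helps decide who may enter, who is removed at 10 months and who is telephoned. At entry it shapes the population that can be randomised. The second application falls at 10 months, the time point of the primary research question. If the printed rule were followed, the total-score arm would remove patients reporting few or no symptoms and would not flag patients reporting many, contrary to the purpose given in Participants, Main study and Ethical aspects.

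**Working it through.** The point turns on the direction of an inequality. The protocol has no power or sample-size figure that depends on it, so there is no stated number to reproduce.

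**Step 1. Apply the printed rule to every possible total.** Inputs: range 0–60 and cut-off below 30, both from the Anxiety and depression section.

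- Whole-number totals available: 60 − 0 + 1 = 61.
- Classed as severe: 0 to 29, which is 30 totals and includes 0.
- Not classed as severe: 30 to 60, which is 60 − 30 + 1 = 31 totals.

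**Step 2. Set the two rules side by side.**

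| Rule | Scores counted as a warning | Direction implied |
|---|---|---|
| Suicide item | 3 and above | higher is worse |
| Total, as printed | 0 to 29 | lower is worse |

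**Step 3. See how much the suicide item would still catch.** Exclusion applies for severe depression or suicide risk, so a high total escapes only if the suicide item is 2 or less. Item ranges are not given. Assume nine items, each scored from 0 to a common maximum m. The largest total with the suicide item at 2 is then 8m + 2:

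- m = 5: 8 × 5 + 2 = 42
- m = 6: 8 × 6 + 2 = 50
- m = 7: 8 × 7 + 2 = 58

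Totals from 30 up to 42, 50 or 58 could therefore pass both arms. This shows which scores are possible. How many patients would have them cannot be derived from the document.

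**Step 4. See whether readers can repair the sign themselves.** A reader who supposes that the sign was reversed still does not know whether a total of exactly 30 counts. Including it gives 31 totals (30–60); leaving it out gives 30 (31–60). The document does not settle this.

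**Step 5. Look for the same pattern elsewhere.** Statistical power sends patients below 7 on any HADS subscale to the reference group. Randomization sends patients below 7 on any HADS subscale to the two trial arms. One condition thus assigns the same patients to two destinations. Statistical power also reports mean scores of 10 and 8 in a group described by a below-7 cut-off, which is hard to square with that description. Intervention – stepped care uses below 7 again as the mark of persistent symptoms.

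**Step 6. Minor check on the range.** 60 / 9 = 6.67. If nine items are scored alike in whole numbers from zero, the maximum is a multiple of 9: 9 × 6 = 54 or 9 × 7 = 63, never 60. Equal scoring is an assumption here.

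**The case against.** The best counter-argument is that this is a lost character and not a rule anyone intended. No plain greater-than sign appears anywhere in the text available for review. The less-than sign stands in the HADS cut-offs where the surrounding text needs the other direction, while the Karnofsky and survival limits in Participants read sensibly. That fits one systematic fault in typesetting or conversion. It is plausible but unproven: the greater-or-equal and less-or-equal signs survive, and the source file cannot be seen. A typographical origin would explain the text without making it usable as a rule.

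A reader might infer several stronger claims that the document does not support:

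- **That all high scorers would be kept without contact.** The suicide item is a second route to exclusion and contact. Main study also provides for a psychologist's contact when forum, diary or chat posts suggest severe depression or suicidality. Only the total-score arm is affected, although posts can alert staff only to patients who write them.
- **That the trial actually screens this way.** Nothing shows how the portal is coded. The stated purpose of the scale makes literal use of the printed sign unlikely.
- **That the 0–60 range is proved wrong.** The arithmetic needs equally scored items, which the document does not state.
- **That the contradiction shows which threshold is right.** It shows only that the statements disagree. The exclusion rule is for the sponsor to state.

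It is also fair to say that the HADS and MADRS-S conflicts may share one cause. The actions differ, however: HADS governs randomisation, the reference group and the offer of step 2, while the MADRS-S governs exclusion and safety contact. Correcting the HADS text alone would leave this rule as it is.

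**Conclusion.** The point holds as an internal contradiction in a decision threshold. As printed, the total-score arm labels 30 of 61 possible totals (0–29) as severe and leaves the other 31 (30–60) unlabelled, against the direction of the suicide item and the purpose given in Participants, Main study and Ethical aspects. This rests on the printed words and on the absence of any other cut-off or mention of reverse scoring.

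The practical effect is limited to the total-score arm and depends on whether anyone works from the printed sign, which the document cannot show. The band of high totals that could still pass (30 up to 42, 50 or 58) depends on assumed item maxima of 5, 6 or 7. A common sign error is the likeliest explanation but is not established. The score-range query is secondary and conditional on equal item scoring.

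**What to change.** 1. Check the printed sign in the Anxiety and depression section against the source file, together with the HADS cut-offs in Statistical power, Randomization and Intervention – stepped care.
2. Reconcile Participants, Anxiety and depression, Main study and Ethical aspects so that the sponsor states one MADRS-S threshold, with its direction and whether the boundary value counts, consistently with the suicide-item rule and the stated purpose of the exclusion.
3. Confirm that the rule coded in the portal matches the reconciled text, both at inclusion and at 10 months.
4. As a minor item, confirm the 0–60 range against the version of the instrument in use and give the item range.

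The cost is a text correction and a check of the portal's scoring code. No extra patients, visits or questionnaires are needed, and the planned 65 and 95 patients per group do not depend on this cut-off.

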### Post-traumatic stress and health-related quality of life

Post-traumatic stress disorder (PTSD) is measured using the PTSD Checklist – civilian version (PCL-C) [36]. The PCL-C consists of 17 questions regarding trauma-related anxiety symptoms. The questions correspond to the diagnostic criteria specified for PTSD in the Diagnostic and Statistical Manual of Mental Disorders, 4th edition (DSM-IV) [37].

Health-related quality of life will be measured using the European Organization for Research and Treatment of Cancer (EORTC) Quality of Life Questionnaire, Core 30 (QLQ-C30) [38], and EORTC diagnosis-specific modules for breast cancer (QLQ-BR23) [39], prostate cancer (QLQ-PR25) [40] and colorectal cancer (QLQ-CR29) [41]. The diagnosis-specific modules are used as supplements to the QLQ-C30. They are all widely used in research projects in cancer care. The core questionnaire, QLQ-C30, consists of 30 questions measuring global health status, quality of life, five features (physical, emotional, cognitive, social, and role functioning) and nine symptoms that are common to all cancers, regardless of diagnosis. The diagnosis-specific modules consists of 23 (QLQ-BR23), 25 (QLQ-PR25) and 29 (QLQ-CR29) questions measuring functions and symptoms that are specific to each diagnostic group.

### Health economy

For the health economic evaluation, data will be collected from several registers, primarily the longitudinal integration database for health insurance and labour market studies (LISA) or LISA’s original records, the patient register, the multi-generation register, the cancer register, the patient register and the pharmaceutical registry as well as other records that may be relevant. Data on health-related expenses not covered by the registry data will be collected via a project-specific health economic survey (HES). The EuroQol EQ-5D [42] will be used for calculation of life-adjusted life years.

